### Interventions

#### Game jam

The intervention will consist of a game jam aimed at creating a low-tech prototype of an educational game to foster cultural safety in medical education. Groups of five or six students or medical interns will create an educational game prototype from scratch. We will follow a six-step game jam protocol based on Macklin’s *Planning your game jam* guidelines[19] (Figure 1).

**
[figure not shown]
Figure 1. Game jam protocol**

1) Preliminary lecture session (one hour): this is comprised of:

(i) A 30 minute lecture on cultural safety will follow a cultural safety curriculum co-designed with local community members knowledgeable about cultural and traditional health practices[20]; and (ii) a 30 minute lecture on game design.

2) Opening ceremony: game jams usually start with opening comments from the host. We will welcome the participants and share the agenda and rules of the game jam.

3) Game building (four hours)**:** this is comprised of six steps:

a) We will invite participants each to write a brief narrative of when they witnessed (or heard of) discrimination or disrespect against a patient because of their traditional health practices, and the consequences of this discrimination.

b) Participants will share their brief stories within their game jam group to discuss and select the story (based on consensus) that best describes discrimination or disrespect against a patient. A key component of this step is to imagine/brainstorm the fullest range of possible consequences – from trivial to life-threatening.

c) Participants will anonymise the selected story as that of a fictional medical student who has to do a primary care clinical rotation in a local community where she/he faces intercultural tensions in clinical practice. The participants will then convert this narrative into a game, and will define a set of rules, rewards, and penalties.

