#### Control

The control group will receive a one-and-a-half-hour lecture on cultural safety in medical education by an expert in cultural safety. The lecture will be a standard lesson using PowerPoint slides and will cover the same key concepts used in the game jam, including (a) definition of cultural safety; (b) consequences of cultural tensions in health care; (c) self-awareness; (d) Colombian cultural health practices; and (e) respect for culturally diverse patients. The lecture will be based on our co-designed curriculum.[25] The session will be followed by a 15-minute period to make comments and to ask questions and a 15-minute break.

After the break, the students will participate in a six-hour workshop based on cultural safety selected readings. Groups of five or six students or medical interns will answer ten open-ended questions based on the lecture and the readings, and will create a poster to graphically display their responses to other students. Similar to the game jam session, we will split each group and encourage a rotation process where participants from all groups will learn from at least two additional posters. Before the end of the session and using Google Forms, we will ask the students to evaluate other groups’ posters in different four categories: creativity, coverage of the topic, graphics and pictures, and layout and design.

In the closing session, the best groups will present their posters to the group at large. In this session, we will unpack and highlight the key concepts of cultural safety. Similar to the game jam session, we will award prizes in the four evaluated categories. Matching that in the intervention, the duration of participation in the control group will be 8 hours.

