### Methods for analyzing data

Primary analysis***:*** using an intention-to-treat approach, we will perform a t-test including 95% confidence intervals to determine the effect of the intervention, including within-group comparisons (baseline and post-intervention I and II) and between-group comparisons (treated versus control post-intervention).

Secondary analysis: we will adjust for sociodemographic baseline variables. We will conduct both a logistic regression and the Mantel-Haenszel procedure, which will allow comparing the results using two different statistical approaches based on different assumptions. Contrary to logistic regression, the Mantel-Haenszel procedure is nonparametric, which makes it free of any statistical assumption and therefore more robust.[44]

Supplementary analysis: both intervention and control arms will engage in group work during the training session. We will use generalised linear mixed modelling (GLMM), paying special attention to a possible cluster enhancement as participants in some study groups generate stronger learning dynamics than others. Additionally, we will follow the methods proposed by [name] and collaborators[24] to conduct probabilistic transitive closure of each CASCADA result chain, which will allow us to explore walks and blocks between intermediate outcomes and to obtain the cumulative net influence. Probabilistic transitive closure is usually conducted on fuzzy cognitive maps where the weights of relationships between concepts are interpreted as probabilities.[45] Every relationship in the map contributes to the summary weight of a walk through a multiplicative function; this approach is appropriate when the number of factors of the model is pre-set.[45]

In our primary analysis, the between-group comparison will yield three *p* values, and the within group-comparison will yield nine *p* values. We will use the Holm procedure to adjust for multiple testing.[46] The Holm method is as robust as the Bonferroni method, but much more powerful.[47]

Non-statistical methods: the students will enter their narratives of change online. Using AtlasTi 8, two research assistants will individually analyze the transcripts following a deductive thematic analysis approach. In deductive analysis, a theory aligned with the researchers’ interest drives the data analysis;[35] we will use the steps described by the CASCADA model to identify themes of change in the stories.

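### The primary t-test ignores work groups of five or six in both arms; if outcomes correlate within groups, its standard errors are too small, and the model that allows for this is only supplementary

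*Protocol*

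**What the plan says.** Under Methods for analyzing data, the primary analysis follows intention to treat: "we will perform a t-test including 95% confidence intervals to determine the effect of the intervention". It covers between-arm and within-arm comparisons. Neither a term for the work group nor a cluster-robust variance is mentioned. The Holm procedure is applied to the resulting p-values, three between arms and nine within arms.

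Both arms are taught in small groups. For the game jam: "Groups of five or six students or medical interns will create an educational game prototype from scratch". For the control: "Groups of five or six students or medical interns will answer ten open-ended questions". Game jam groups build for four hours and refine for another half hour. Control groups share a six-hour workshop.

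The supplementary analysis recognises this. It notes that "both intervention and control arms will engage in group work during the training session" and plans a generalised linear mixed model, "paying special attention to a possible cluster enhancement as participants in some study groups generate stronger learning dynamics than others". The Sample size section contains neither an ICC nor a design effect.

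**The concern.** If some groups learn better together than others, members of one group share a component of the outcome. That is within-group correlation, and it arises after randomisation, so individual allocation does not remove it. A t-test on individuals then counts more independent information than the data hold: the p-value comes out too small and the interval too short.

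The Protocol names this mechanism and has a model for it, but rests the primary inference on the test that excludes it. If the two analyses disagree, the stated hierarchy favours the t-test. In a superiority trial that error leans towards a false positive on the primary outcome. This is a ranking that the Protocol fixes itself, not a detail left to a statistical analysis plan.

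**Working it through.** **Inputs from the Protocol.** Group size 5 or 6 in both arms (Interventions), so a mean of m = 5.5. Two-sided alpha 0.05, difference 26.9 − 25.9 = 1.0, SD 4, d = 0.25, 199 per arm (Sample size). 640 randomised 1:1 (Results), so about 320 per arm.

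**Assumption.** No ICC is given. The range 0.02 to 0.10 is assumed.

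**The plan's own figure.** With no clustering, d = 0.25 at two-sided 0.05 and 80% power needs 252 per arm (normal approximation) or 253 (exact t). At 199 per arm the power is 0.70. The figure 199 is reproduced by a one-sided 5% test (exact t, power 0.801). That mismatch is a separate matter. It matters here only because power at 199 starts from 0.70 and not from 0.80.

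**Formulas.**
- Design effect: DE = 1 + (m − 1) × ICC.
- True error of one nominal 5% test: 2 × [1 − Φ(1.96/√DE)].
- Shortfall in interval width: 1 − 1/√DE.
- Power of a cluster-adjusted test: the usual two-mean power with n/DE per arm.

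| ICC | DE | √DE | True error | Coverage of 95% CI | CI too narrow by | Adjusted power, 199 per arm | Adjusted power, 320 per arm |
|---|---|---|---|---|---|---|---|
| 0 | 1.000 | 1.000 | 0.050 | 95.0% | 0% | 0.70 | 0.88 |
| 0.02 | 1.090 | 1.044 | 0.061 | 94.0% | 4% | 0.67 | 0.86 |
| 0.05 | 1.225 | 1.107 | 0.077 | 92.3% | 10% | 0.62 | 0.82 |
| 0.10 | 1.450 | 1.204 | 0.104 | 89.6% | 17% | 0.54 | 0.75 |

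Example at ICC 0.10: DE = 1 + 4.5 × 0.10 = 1.45; 1.96/1.204 = 1.628; 2 × [1 − Φ(1.628)] = 0.104.

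**Check by simulation.** With 40 groups of five per arm and no true effect (10,000 trials), the plain t-test rejected in 5.1%, 7.2% and 9.3% of trials at ICC 0, 0.05 and 0.10. For m = 5 the formula gives 5.0%, 7.4% and 9.8%.

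**The Holm step.** If Holm is run over the three between-arm p-values, its first threshold is 0.05/3 = 0.0167 (z = 2.394). The true error at that threshold is 2 × [1 − Φ(2.394/√DE)], which is 2.2% at ICC 0.02 and 4.7% at ICC 0.10, instead of 1.67%. The inflation passes through Holm.

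**The case against.** The best defence is that the plan does not overlook the issue. It names the group work in both arms and prespecifies a mixed model, so a cluster-adjusted result will be reported. That is true, and it makes the remedy easy, but a supplementary result does not set the primary p-value or interval.

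A second defence is individual randomisation. It does protect against similarity among students that existed before allocation. It does not protect against variation that the group session creates.

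Third, students rotate through at least two other groups' games or posters, and lectures and closing sessions are shared by the whole arm. This mixing may lower the ICC and is a fair reason not to assume a large one. It does not dissolve the home group in which most of the work is done.

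Several stronger readings are tempting and are not supported:
- That the p-values and intervals certainly are too optimistic. The Protocol speaks only of a possible effect and gives no ICC. At zero ICC nothing is wrong, and at 0.02 the effect is minor.
- That 6% to 10% is the trial's overall error rate. It is the error of one unadjusted 5% test, and the plan applies Holm.
- That clustering alone takes power from the stated 0.80 to 0.54 at 199 per arm. The fall from 0.80 to 0.70 has the separate cause given above.
- That student-to-group membership is already on file. Attendance records hold names, date, hour and signatures, and game jam groups register their game. No statement says that each student's group is recorded, and no equivalent registration is described for the control arm.

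**Conclusion.** The point holds conditionally. The direction is certain for any positive within-group correlation arising in the sessions, which the Protocol itself regards as possible. The size rests on the assumed ICC: slight at 0.02, and material from about 0.05, where one nominal 5% test has a true error near 8% and the interval is about 10% too narrow. Neither Holm nor the covariate-adjusted secondary analysis, as described, corrects the primary standard error, and the multiple imputation has no stated group structure.

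The figures suit the comparison immediately after the session best. The primary outcome also runs to six months, and the documents do not show whether a group effect would persist, so the same ICC cannot be assumed there. Within-arm changes are exposed to the same problem but are not quantified here.

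**What to change.** Make the primary between-arm analysis a linear mixed model for the cultural safety score, with arm as a fixed effect and a random intercept for work group in both arms. Use small-sample degrees of freedom, and enter randomised students who never joined a group as singletons, so that the intention-to-treat set stays whole. Report the ICC, and keep the plain t-test as a sensitivity analysis.

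Two further steps are needed. Confirm that each student's work group is recorded in both arms, which the planned mixed model already requires. Make the Amelia II imputation compatible with the group structure, since none is described.

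The cost is mainly a change to the analysis text, plus the work on the imputation. The interval becomes somewhat wider. With 320 per arm, before attrition, power for d = 0.25 would be about 0.86 to 0.75 over the assumed ICC range, against 0.88 with no clustering. If the ICC turns out near zero, the result will hardly differ from the t-test.

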Fowler and collaborators recently found that game jam participation could improve computing students' performance.[15] We are not aware, however, of any reported experience using game jams to train medical students. Our primary objective is to determine whether medical student participation in a game jam to design an educational game on cultural safety is more effective than a standard lesson on cultural safety in terms of change in students’ self-reported intended patient-oriented behavior. Our secondary objectives are to: (i) determine the impact of the intervention (game jam) compared with the control (standard lesson on cultural safety) on students’ confidence in their general transcultural skills; and (ii) assess the impact of participation in the game jam through a narrative approach that identifies in their own words the effect of the learning on cultural safety in their clinical practice.

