### Outcomes

Primary outcome: our primary outcome will be students’ self-reported intended patient-oriented behavior. Our outcome is self-reported because it uses students’ opinion regarding their perceived change; intended, because we are assessing students’ planned behavior instead of actual practice/action; and patient-oriented because we measure responses to clinical scenarios indicating intended behavior change. We will assess intended behavior change from the baseline to immediately following the teaching session, from immediately following the teaching session to six months post-intervention, and from the baseline to six months post-intervention.

We will use the CASCADA model of planned behavior to inform our primary outcomes.[22] The model includes the following variables: **C**onscious knowledge was the response to the statement: Considering the cultural beliefs of my patients is not important for health-decision making. **A**ttitude to cultural safety was derived from the statement: It is not worth considering the cultural beliefs of my patients to improve their health. **S**ubjective norm used the statement: Although many physicians disapprove cultural beliefs, I think that these beliefs could improve my patients’ health. Intention to **C**hange derived from the statement: I do not think that learning about cultural beliefs is necessary to provide good health care to my patients. **A**gency was the response to the statement: I feel prepared with the knowledge and skills to prudently incorporate my patients' cultural practices in the health-decision making process. **D**iscussion derived from the response to the statement: I will discuss cultural safety with other students and physicians so they can prudently incorporate their patients' cultural practices in the health-decision making process. Agency and Discussion replace perceived behavior in a conventional theory of planned behavior.[23] Agency involves both self-efficacy and collective efficacy. The CASCADA model includes Discussion as an additional factor that facilitates behavior change.[24] **A**ction was the response to the statement: I will never be open to include my patients’ cultural beliefs and practices in the health-decision making process. Participatory research experts have successfully used the CASCADA model to explore dengue prevention behavior in previous trials.[24]

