Secondary outcomes: (i) students’ confidence (transcultural self-efficacy) in their general transcultural skills; and (ii) qualitative understanding of the impact of the intervention in the clinical practice of medical students and medical interns through the Most Significant Change Technique. We will assess transcultural self-efficacy in the baseline, immediately following the teaching session, and six months post-intervention, and we will conduct the qualitative assessment in both groups six months after the intervention.

Output: each student group of the intervention arm will create a co-designed low-tech prototype of a serious game to foster cultural safety in medical students. Some of these prototypes may serve as blueprints for future fully developed games, or as input for future educational videogames.

In addition to the quantitative outcomes of the RCT, we will use the qualitative Most Significant Change narrative technique[25] to collect and analyze stories of change from the medical students six months after the intervention. This technique will allow us to capture meaningful changes in the students’ clinical practice, which may not be apparent from the quantitative evaluation.

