For the third part of the instrument (cultural safety), we developed a Likert-type preliminary version based on our CASCADA variables (see primary outcome) and piloted it for validity and reliability in our pilot RCT.

Validity and reliability: using data from our pilot RCT, we followed the process proposed by Jeffreys[34] to improve the validity and reliability of the third part of our instrument. In the pilot study, the questionnaire included the open question: *how can we improve this instrument?* An inductive thematic analysis[35] of responses identified suggestions to adjust our survey. We shared the adjusted version of the instrument by email with two general practitioners, one medical intern, six medical students, and four cultural safety experts. We adjusted the instrument according to their comments and agreed on the content validity of the instrument by consensus.

To increase the construct validity of our instrument, we used the contrasted group approach, which explores the difference between two separate groups.[34] To increase the predictive validity of our instrument, we looked at the score difference between two timeponts.[36] Reliability explores the degree of accuracy and consistency in measurement. Using R Studio v1.1.419, we calculated Cronbach’s alpha[37] to determine the internal consistency of our instrument. Since our instrument was short (<10 items), we expected a value of >0.5.[38] We complemented the reliability exploration using the test-retest method to explore the stability of the instrument.[34] We report the validity and reliability results of our instrument in the pilot RCT, which is not yet published.

Qualitative data to be collected: to explore students’ stories of change after cultural safety training, we will use the Most Significant Change approach, which is a narrative technique that allows participants to communicate changes most meaningful to them.[39] Using a pre-defined format in Google forms, we will ask participants to write down and enter their stories based on the following questions: *(a) what do you believe was the most significant change in your clinical practice as a result of your participation in the activity [game jam or standard lesson] 6 months ago? (b) can you please share a real-life story depicting this change? (c) why do you think this story is significant?*

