The instructions will make clear that participants should feel free to write down stories of negative changes or to say that they did not experience any change at all. Only medical students involved in clinical practice and medical interns (third to seventh year of medical school) will be invited to participate in this part of the RCT.

Methods to maximise completeness and quality of data: The study coordinator and facilitators will be physically present while collecting the data at each time point to ensure the completeness of data. Additionally, we will use several validation options to increase the quality of the data: specific number range, specific character range, date validation, email address format, and prompts that alert participants when they enter incomplete or invalid answers.

In this study, the familiarity of millennial medical students with technology and computer-based education supports using Web-based questionnaires, which reputedly decrease social desirability bias.[40] Assured of anonymity, respondents should be less concerned about what others may think about their responses, including peers and professors.[41] Data reliability in Web-based questionnaires is reportedly equal to or better than traditional paper-based approaches.[42] Examples include data on self-reported perceived health status, oral contraceptive use, and smoking and alcohol use. Web-based questionnaires are also faster to complete and typically cheaper than traditional approaches, making them ideal for our research.

Methods for ensuring secure storage of data: SurveyMonkey and Google responses are stored in a worksheet that can only be accessed through an account login. Data transmission uses Secure Sockets Layer to encrypt information during transport. The data storage is as secure as most other systems that store survey information. After downloading the data, we will delete it from SurveyMonkey and Google Forms. We will be responsible for ensuring the data are securely stored for seven years and then destroyed in accordance with CIET guidelines for security, storage, and eventual destruction of data records.[43]

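### The stories are meant to show practice changes that the questionnaire misses, but the only coding frame stated is the questionnaire's own CASCADA model, with no category for negative, absent or out-of-model change

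*Protocol*

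**What the plan says.** **Purpose.** The secondary objectives, at the end of the Introduction, describe "a narrative approach that identifies in their own words the effect of the learning on cultural safety in their clinical practice". The Outcomes section says the technique is there to "capture meaningful changes in the students’ clinical practice, which may not be apparent from the quantitative evaluation". Under Trial design, reported change in clinical practice is part (c) of the question put to the randomised comparison. Stories are collected in both arms at six months.

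**Invitation.** Under Data collection methods, the instructions will tell writers that "participants should feel free to write down stories of negative changes or to say that they did not experience any change at all".

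**Coding.** Under Methods for analyzing data (Non-statistical methods), "two research assistants will individually analyze the transcripts following a deductive thematic analysis approach". The protocol explains a deductive analysis as one driven by a theory that fits the researchers' interest, and names the theory: "we will use the steps described by the CASCADA model to identify themes of change in the stories".

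**The same model elsewhere.** On the primary outcome, the Outcomes section says: "We will use the CASCADA model of planned behavior to inform our primary outcomes". It then lists seven elements: conscious knowledge, attitude, subjective norm, intention to change, agency, discussion and action. Data collection methods states that the third part of the questionnaire was built from these same variables.

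**The concern.** The stories are justified by what the questionnaire may fail to show, yet the plan reads them through the model on which the questionnaire is built. A theme that does not belong to one of the seven elements has no stated place. Nor does a story of harm, or a statement that nothing changed, although the instructions ask for both.

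Three things are at stake.

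- Unexpected changes in practice could be left out or absorbed into the nearest CASCADA element.
- Null and negative experiences could go uncounted. Because both arms write stories, a difference between arms in such experiences could go unseen, and that bears directly on part (c) of the research question.
- Agreement between stories and questionnaire would owe something to the shared frame. A reader could take it for more independent support than it is.

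The stories also carry some weight in the protocol's own argument. The Discussion explains that patient-related outcomes are beyond the trial's capacity and points to the stories as part of the impact assessment.

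**Working it through.** No figure in the protocol bears on this point, so there is nothing to recompute. The check sets the stated purpose and the invited content beside the stated analysis.

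| What the stories may contain | Where the protocol asks for it | Place in the stated coding |
|---|---|---|
| Practice change that fits a CASCADA element | Outcomes; story prompts in Data collection methods | Yes, under that element |
| Practice change outside the seven elements | Outcomes (changes the quantitative evaluation may not show) | None stated |
| Negative change | Instructions in Data collection methods | No direction code stated; could be placed under an element at the coder's discretion |
| No change | Instructions in Data collection methods | None stated |

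1. **Is another frame or step stated?** The paragraph on non-statistical methods names deductive thematic analysis and the CASCADA steps. It mentions no inductive step, residual category or code for direction. The team knows the inductive method: Data collection methods reports an inductive thematic analysis of pilot responses, used to revise the instrument.

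2. **Is the frame shared with the questionnaire?** Yes. The seven elements define the primary outcome, and the third part of the instrument is built on them.

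3. **Does the shared frame make the stories redundant?** No. The Outcomes section says the questionnaire records what students plan to do and not what they have done. The prompts ask, six months later, for the most important change in clinical practice and a real example. A story coded to action or discussion can therefore report conduct that the questionnaire does not measure.

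4. **Can the elements hold a negative change?** In principle, yes. Four of the seven questionnaire statements are worded against cultural safety (conscious knowledge, attitude, intention to change, action), so the constructs run in both directions. But the plan looks for themes of change, and nothing tells two coders working individually to record the direction, or to record that there was none.

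Steps 1 and 2 establish the mismatch. Steps 3 and 4 limit it: the coding may lose part of what the stories were added to provide, but not all of it.

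**The case against.** The strongest reply is that the protocol names a frame without closing it. It does not say that other codes are excluded or that stories which do not fit are dropped, and a codebook held elsewhere could contain the missing categories. Deductive coding is a legitimate choice, and the protocol gives a reason for it. The reference to participants' own words concerns how the narratives are obtained, and the open prompts deliver that; every thematic analysis then applies the analyst's themes.

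Much of this stands. A reader might infer that the coding is confined to CASCADA and so can only repeat the domains of the primary outcome, or that negative and null stories will be forced into a favourable step and tilt the result towards benefit. The documents support neither inference. Silence about other codes is not exclusion, stories of actual practice differ from scores of planned behaviour, and an element can hold a change in either direction.

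What does not stand is the suggestion that this is merely detail left for later. The protocol itself fixes the approach and the frame, and does so in a way that fits poorly with the purpose it gives for the stories and with the content it asks participants to supply.

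**Conclusion.** The point holds in a limited form. The only coding frame stated for the stories is the model the questionnaire already uses, with no open coding and no category for negative, absent or out-of-model change. Followed as written, the analysis may miss or blur those experiences and any difference between arms in them.

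Its size cannot be given as a number, because the protocol offers no basis for the share of stories that would be null, negative or outside CASCADA. It affects one secondary outcome, which is also part (c) of the research question, and does not touch the primary analysis. The conclusion assumes that the coders apply the frame as the protocol describes it, without further instructions. If a coding manual already provides these categories, the protocol need only say so.

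**What to change.** In the paragraph on non-statistical methods under Methods for analyzing data:

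- keep the CASCADA steps as the deductive frame;
- add a direction code for each story: positive, negative or no change;
- add a category for change outside CASCADA, with its content coded inductively;
- report the number of stories under each code by arm.

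This takes a sentence or two in the protocol and some additional coding time for the same two research assistants. It needs no new data and no further staff. The drawback is a thematic frame somewhat less tidy than one drawn from a single theory.
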